## Abstract

**Background:**

In the Netherlands, suspected cases of child maltreatment can be reported to an advice and reporting center on child abuse and neglect (Advies- en Meldpunt Kindermishandeling or AMK). AMKs investigate these reports, screen for problems in the family and its surroundings and refer to child welfare. Over the last decades the focus of AMK investigations has changed from an adult-only approach to a more child-oriented approach using a Child-Interview intervention. The effects and cost-effectiveness of AMK involvement in the Netherlands have never been studied. The primary aim of this study is therefore to examine the effect of the participation of maltreated children aged 6–18 years in the Child-Interview intervention on their mental health and quality of life. As a second aim, this study will examine the balance between additional costs and effects of the Child-Interview intervention in comparison with AMK investigation without the Child-Interview intervention (adult-only intervention).

**Design/Methods:**

A quasi-experiment will be performed consisting of two post-intervention measurements of two nonequivalent groups: an intervention group, in which the Child-Interview intervention has been used during the AMK investigation, and a control group, in which the intervention has not been used (adult-only intervention). Participants from an ongoing prospective study on the mental health and quality of life of maltreated children after a report to an AMK, will be contacted to complete a questionnaire twice. Multivariate regression analyses will be used to determine effectiveness of the Child-Interview intervention. The economic evaluation will involve a cost-effectiveness analysis and a cost-utility analysis.

**Results/Discussion:**

This will be the first study to examine the effect of AMK involvement in the Netherlands. Using the Child-Interview intervention during AMK investigation may prevent or reduce negative outcomes of child maltreatment, which may result in a lower consumption of healthcare and other services. In addition, the importance of economic evaluations is increasingly recognized, and economic evaluations about child maltreatment are scarce. Limitations include the risk of potential recall bias and selection bias.

**Trial registration:**

NTR3728, funded by ZonMw, project 15700.2012

## Background

It is commonly known that child maltreatment has a huge impact on the lives of children and adults, as it is associated with both short- and long-term adverse life outcomes [1,2]. Studies have repeatedly shown the negative impact of child maltreatment on general and mental health [3-6] and quality of life [7-9].

The prevalence of child maltreatment in the Netherlands in the 0–18 years age range has been estimated at 34 per 1,000 children in 2010 [10]. In the Netherlands, suspected cases of child maltreatment can be reported to an advice and reporting center on child abuse and neglect (Advies- en Meldpunt Kindermishandeling or AMK), both by professionals and non-professionals, through a voluntary reporting system. The annual number of reports of suspected child maltreatment to these AMKs increased by 37.5% between 2006 and 2011 [11,12]. The AMKs investigate these reports and screen for problems in the family and its surroundings. If the report is substantiated, the AMK takes appropriate action, such as referring the child and family to child welfare and/or mental health organizations that can provide the necessary care. If voluntary care is rejected, the AMK can report the family to child protection services that can take court action or arrange the child to be placed in care outside the home. In case of substantiated violence, the AMK may file a report to the police [13].

Over the last decades the focus of the AMK investigations has changed from an adult-only approach to a more child-oriented approach using a Child-Interview intervention. In the adult-only intervention, only adults, including parents, teachers and general practitioners, are asked to provide information to substantiate the alleged abuse. Children are not used as informants in this intervention, for two reasons: the belief that children could not provide reliable and accurate information and the belief that children should not be troubled with questions about maltreatment. Regarding the first reason, several studies have shown that children can be reliable informants [14-17]. The Child-Interview intervention includes children aged 6 years and over as informants in the AMK investigation, in addition to adult informants. The children are interviewed by an AMK employee. Just as in the adult-only intervention, the aim of this interview is to collect information on the alleged child maltreatment, the existence of any family problems, the child’s needs for help and/or protection and the willingness to accept help and/or protection. An additional aim is to increase the child’s sense of being in control. AMK workers have confirmed the value and relevance of this information provided by children. In their experience, the maltreated children can provide highly relevant information that is otherwise not retrieved and this Child-Interview intervention therefore results in potentially better tailored interventions.

Regarding the second reason, several studies have shown positive effects on the children of talking about their maltreatment experiences. These studies showed that talking about such experiences may be the start of the recovery process and may increase children’s feelings of control and self-esteem [18-20], whereas keeping maltreatment experiences a secret is associated with additional trauma [21,22]. These findings suggest that the Child-Interview intervention is not only helpful for the referral to well-tailored care, but there are also benefits for the mental health and quality of life of these maltreated children. Nowadays all AMKs in the Netherlands have adopted the Child-Interview intervention and this is the preferred method according to the AMK manual [13]. Nevertheless, AMK records show that the adult-only intervention is still used in many AMK investigations. Little research has been done on the effects of specific AMK interventions [23], and scientific evidence on the presumed superiority of this Child-Interview intervention in comparison to an adult-only intervention is lacking.

In addition, it is well documented that children who have been abused or neglected are more likely to experience adverse outcomes in a number of domains throughout their lives. This results in an increasing demand on multiple services, including healthcare, by both children and their families [23]. Studies in the US have shown that substantial costs are associated with the impact of child maltreatment [24,25]. In the Netherlands, Meerding [26] estimated the economic burden of child maltreatment to be 965 million euros in 2003, which is about 138 euros per household annually. This was probably an underestimation, however, because the prevalence of child maltreatment in the Netherlands had not been studied yet and the estimates used were much lower than the recent prevalence rates reported by Alink and colleagues [10].

Due to scarcity of resources, the importance of economic evaluation studies has been increasingly acknowledged over the last decade. These studies provide information on the impact of child maltreatment on society and the costs of its treatment, which will help identify cost-effective resources. This knowledge contributes to informed decisions on the funding of services and to policy improvements [27,28]. So far, however, economic evidence on child maltreatment is scarce [27,29]. Corso and colleagues performed two literature reviews [27,29] and found that existing studies have focused mainly on cost of illness and do not include loss of quality of life. To our current knowledge, there have been five economic evaluations relating to child maltreatment, i.e. studies in which two or more interventions were analyzed in terms of the costs of effects. Three of these economic evaluations concerned prevention programs for parents [30-32]. The other two studies focused on sexually abused children in secondary care [33,34]. Economic evidence on the impact of child maltreatment and economic evaluations looking at interventions in this field have been scarce, especially in a Dutch context. The societal costs and effects of AMK involvement in the Netherlands have never been studied, even though AMKs have a pivotal function in stopping maltreatment, and thus in reducing its prevalence. Therefore, the primary aim of this study is to examine the effect of the participation of maltreated children aged 6–18 years in the AMK investigation (Child-Interview intervention) on their mental health and quality of life. As a second aim, this study will examine the balance between additional costs and effects of the Child-Interview intervention in comparison with AMK investigations without this intervention (adult-only intervention), from a societal perspective.

## Design/methods

### Study design

To answer the research questions, a quasi-experiment will be performed in which respondents from an ongoing prospective study on the mental health and quality of life of maltreated children after a report to an AMK [35] will be asked to complete an additional questionnaire at follow-up assessments. The quasi-experiment will consist of two post-intervention assessments of two nonequivalent groups (intervention group and control group) (see Figure 1). The study sample of the prospective study consists of maltreated children and their primary caretaker. These parent–child dyads were recruited for participation in the prospective study during the AMK investigation following a report to an AMK. Based on information from AMK records, the study sample will be divided into two groups: an intervention group, in which the Child-Interview intervention was used during the AMK investigation, and a control group, in which the intervention was not used (adult-only intervention).

**Figure 1 F1:**
[figure not shown]
**Flow chart of quasi-experimental study design.***Note. Assessment 1 and 4 of the prospective study have no connection with the quasi-experiment.*

The gold standard for experimental and effectiveness and cost-effectiveness studies is a randomized controlled trial (RCT), in which participants are divided to two study groups based on random assignment. The Dutch Medical Ethics Committee for Mental Health Care (METiGG) did not approve of a RCT, because randomization might result in a parent–child dyad receiving a suboptimal approach (in this case the adult-only intervention), which the committee decided was not ethically acceptable in the case of vulnerable young children. Although evidence on the adult-only intervention is lacking, this is supported by Article 33 of the Declaration of Helsinki. This article states that it is not acceptable to withhold treatment/intervention when it is known that this treatment can be lifesaving or that abstinence might lead to irrecoverable damage to the subject [36].

While preparing for the study, however, we found from AMK records that although the Child-Interview intervention is the preferred method according to the AMK manual [13], the Child-Interview intervention was not used during the investigation in a substantial number of AMK investigations. This enabled us to propose a quasi-experimental design in which an existing study sample (from the prospective study mentioned above) was divided into two groups based on the intervention they had received during the AMK investigation. Data collection for the quasi-experiment could be incorporated in this prospective study (see Figure 1). This design would make it possible to answer the research questions without randomization, though a disadvantage of this design is the possibility of selection bias. The economic evaluation will involve a combination of a cost-effectiveness analysis (CEA) and a cost-utility analysis (CUA).

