### Assessment

This study will consist of two assessments: A and B (see Figure 1). Assessment A will take place at the same time as assessment 2 of the prospective study (6 months after the AMK investigation). Assessment B will take place six months later, at the same time as assessment 3 of the prospective study (12 months after the AMK investigation).

At assessments A and B, children and parents will be asked to complete a questionnaire. A member of the research team will meet the parent and child at a place of their choice (in most cases their own home) to assist them. The way in which the questionnaire is to be completed will be discussed with the parent and the child, and will depend on the participants’ reading and writing skills. If reading and writing skills are poor, a research team member will read out the questions and write down the participant’s answer on the questionnaire form. If reading and writing skills are sufficient, participants may choose to complete the questionnaire by themselves. To prevent the parents from influencing the children’s answers, parents and children will be requested to complete their questionnaires in separate rooms. Respondents will be rewarded for their participation by a 10 euro gift voucher for the parents, while the children will receive either a 5 euro gift voucher (children > 10) or an age-appropriate present (6–10 years).

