### Analyses

Data will be analyzed according to the intention-to-treat principle. The similarity of baseline characteristics (socio-demographic characteristics, costs and outcomes) between the two AMK investigation interventions will be examined using univariate tests and Chi-square tests. Loss-to-follow up will be accounted for by imputing missing data using regression imputation.

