#### (1) Effectiveness study

A multivariate regression analysis will be performed in which outcomes of mental health and quality of life will be compared between the Child-Interview intervention group and the control group (adult-only intervention). This will be done at follow-up (assessment B), 6 months after assessment A and a year after the intervention. Covariates will be taken into account.

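### The planned comparison of baseline costs and outcomes has no pre-intervention data behind it: the earliest values in the study are six months after the intervention

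*Protocol article*

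**What the plan says.** All references are to the protocol article.

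- **Study design:** "The quasi-experiment will consist of two post-intervention assessments of two nonequivalent groups (intervention group and control group". The dyads "were recruited for participation in the prospective study during the AMK investigation following a report to an AMK".
- **Assessment:** "Assessment A will take place at the same time as assessment 2 of the prospective study (6 months after the AMK investigation"). Assessment B follows six months later, "at the same time as assessment 3 of the prospective study (12 months after the AMK investigation").
- **Note to Figure 1:** "Assessment 1 and 4 of the prospective study have no connection with the quasi-experiment".
- **Analyses:** "The similarity of baseline characteristics (socio-demographic characteristics, costs and outcomes) between the two AMK investigation interventions will be examined", using univariate and chi-square tests.
- **Analyses, (1) Effectiveness study:** groups are compared at B, and "Covariates will be taken into account". The covariates are not named.
- **Quality adjusted life years (QALYs):** the gain is the change in utility from A to B multiplied by the duration of the effect.
- **Discussion:** a multidisciplinary team chooses the approach, and the authors accept that the groups may differ at the start.

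**The concern.** In a non-randomised comparison, a baseline check is there to show whether the groups differed before exposure. For costs and outcomes, this plan has no data from before exposure. The only source inside the study is A, by which time the intervention has had six months to act. A test at A mixes prior difference with effect and cannot say which it sees.

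Two errors could follow. A real early benefit might be read as imbalance and adjusted away. Or similarity at A might be reported as evidence of comparable groups when a prior difference and an effect had cancelled. In either case the concern about internal validity raised in the Discussion would look answered when it was not.

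**Working it through.** **Step 1: can any in-study cost or outcome be a baseline?**

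| Source | Timing | Pre-intervention? |
|---|---|---|
| Assessment A | 6 months after the investigation | No |
| Assessment B | 12 months after the investigation | No |
| Assessment 1 of the prospective study | Before A; exact time not stated | Unknown, and excluded by the Figure 1 note |

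If the baseline values come from A, they are not baseline. If they come from assessment 1, the Figure 1 note is wrong. The text has to change on either reading. Socio-demographic characteristics are not affected.

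**Step 2: what an unmeasured prior gap does at B.** The plan gives no figure on this. Inputs from the document are the target d = 0.45, alpha 0.05 one-tailed, 117 dyads, and about 40% adult-only investigations, giving 70.2 against 46.8. The prior gap g (in SD) and the correlation r between the prior score and B are not in the document. I assume g = 0.2 to 0.5 and r = 0.5 to 0.7, with equal SDs and no other covariate capturing the gap.

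- Bias at B = r × g. Lowest: 0.5 × 0.2 = 0.10 SD. Highest: 0.7 × 0.5 = 0.35 SD.
- As a share of 0.45: 0.10/0.45 = 22%; 0.35/0.45 = 78%.
- SE of the group difference = √(1/46.8 + 1/70.2) = 0.189 SD.
- One-sided type I error if there is no true effect = Φ(bias/SE − 1.645), which is 13% at 0.10 and 58% at 0.35, instead of 5%.
- If the bias runs against the intervention and the true effect is 0.45, power = Φ((0.45 − bias)/SE − 1.645). It falls from 77% without bias to 58% and 13%.

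**Step 3: what would happen if A were used as the baseline covariate.** The plan does not state this; the calculation shows why it should be ruled out. With a true effect of 0.45 SD at both A and B and correlation r between them, the expected adjusted coefficient is 0.45 × (1 − r):

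- r = 0.5: 0.225 SD
- r = 0.6: 0.18 SD
- r = 0.7: 0.135 SD

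**Step 4: the QALY formula.** Here the plan does use A as its reference point. If the intervention group's utility is higher by u at A and still higher by u at B, the difference in change is u − u = 0. A benefit reached by month 6 and kept to month 12 counts as no QALY gain, while the cost side of the ratio uses annual costs.

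**Separate matter.** The plan's one computed figure, 110 dyads, is not used above and does not reproduce. At d = 0.45, n per group = 2 × (1.645 + 0.842)²/0.45² = 61.1, rounded up to 62, or 124 in total at 1:1. Nothing in this point depends on it.

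**The case against.** The strongest reply is that the authors are open about the design. They call both assessments post-intervention and the groups nonequivalent, and they name selection bias as a limitation. An unnamed covariate list is something an article commonly leaves to the full plan. Both points stand, and the bare mention of covariates is not counted here as a fault. General disclosure does not, however, reconcile a design with only post-intervention data with a promised baseline comparison of costs and outcomes.

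Three stronger readings are tempting, and the document does not support them.

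- A reader might infer that assessment 1 is a clean pre-intervention CBCL and PedsQL score that the plan throws away. The document gives neither its timing nor its content, and Figure 1 is not shown. Recruitment took place during the investigation, which is also when the child is interviewed, so assessment 1 may fall on either side of the interview. That the parent study concerns mental health and quality of life makes it a candidate and no more.
- A reader might infer that the effectiveness analysis adjusts for A or uses change from A. The section on that analysis says neither; only the QALY calculation uses the A-to-B change.
- A reader might infer that control of confounding is lost altogether. Socio-demographic and record-based covariates remain available, and some reasons the Discussion gives for adult-only investigations, such as parental refusal or language barriers, would not be captured by an earlier outcome score anyway.

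It is also fair to say that adjusting for an assessment 1 taken after the interview would remove part of the effect, as adjusting for A would. The fix has to allow for that.

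**Conclusion.** The point holds in limited form. As written, the baseline comparison of costs and outcomes cannot do its job, because the only such values the plan admits are 6-month post-intervention results. This follows from the article's own timeline and needs no assumption.

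The consequence for the comparison at B is a possible bias of 0.10 to 0.35 SD. That range rests wholly on the assumed prior gap and correlation and shows scale only; the document gives no evidence of an actual gap or of its direction. How much an earlier score could reduce the bias depends on what assessment 1 contains and when it was taken. Should be fixed; confidence medium.

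**What to change.** 1. **Analyses section.** Limit the baseline comparison to characteristics fixed before the investigation: socio-demographic and AMK-record variables. Report outcomes and costs at A as 6-month results. State that A values are not covariates for the group effect at B.
2. **Figure 1 note.** State the timing and content of assessment 1. If it holds CBCL and PedsQL, amend the note so that these scores are linked and used as covariates at B. Define timing the same way in both groups, for example relative to the report date or to the start or end of the AMK investigation. The interview date will not serve, because adult-only cases have no interview. Where assessment 1 may have followed the interview, report results with and without this adjustment and say that it may remove some early effect.
3. **Economic evaluation.** State that pre-intervention costs and utilities may not be recoverable, since this study adds its questionnaire only at the follow-up assessments. State also that the A-to-B QALY change misses any effect reached by month 6.

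The cost is redrafting and some data linkage within one cohort, subject to checking that the consent given covers it. Residual confounding from the team's choice of approach remains whatever is done.

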### Assessment

This study will consist of two assessments: A and B (see Figure 1). Assessment A will take place at the same time as assessment 2 of the prospective study (6 months after the AMK investigation). Assessment B will take place six months later, at the same time as assessment 3 of the prospective study (12 months after the AMK investigation).

At assessments A and B, children and parents will be asked to complete a questionnaire. A member of the research team will meet the parent and child at a place of their choice (in most cases their own home) to assist them. The way in which the questionnaire is to be completed will be discussed with the parent and the child, and will depend on the participants’ reading and writing skills. If reading and writing skills are poor, a research team member will read out the questions and write down the participant’s answer on the questionnaire form. If reading and writing skills are sufficient, participants may choose to complete the questionnaire by themselves. To prevent the parents from influencing the children’s answers, parents and children will be requested to complete their questionnaires in separate rooms. Respondents will be rewarded for their participation by a 10 euro gift voucher for the parents, while the children will receive either a 5 euro gift voucher (children > 10) or an age-appropriate present (6–10 years).

